### Outcomes and measures

#### Primary outcomes

The level of depressive symptomatology and a categorical diagnosis of depression after treatment constitute the primary outcomes.

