**CONSORT flow diagram**[94]**showing subject allocation to the therapy conditions.**

### Sample size

An *a priori* power analysis based on a medium effect size estimation indicated that a total of 100 participants are needed (planned main statistical test is ANOVA (repeated measures, between factors); *f* effect size: 0.247; statistical power: 0.80; α error probability: 0.05; two groups, two main measurements (pre-intervention and post-intervention); correlation between repeated measures: .50). Power analysis was computed using the G*Power 3.1.6 program [95]. Consequently, we randomized a total of 100 participants. Following generation of the random numbers, we decided to use the first sequence of numbers for the participants’ allocation to the groups. This resulted in 43 participants randomized to the CT group, and 57 participants randomized to the ED-CT group.

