The severity of, and improvement in the BDI-II scores within and between the groups will be examined using mixed-effects linear regression analysis with a random intercept and slope over time (four assessments: baseline, after sessions 4 and 8, post-treatment) and fixed effects for treatment assignment.) The 3-month follow-up data will be analyzed in a separate mixed-effects model. The main analysis will compare groups in terms of depression level (that is, diagnostic status and symptom intensity). Results on the other measures will be investigated in an exploratory manner. When analysis of secondary/other outcomes are performed, the error probability will be adjusted according to the number of group comparisons performed [98].

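### Two primary outcomes are compared with no stated success rule, and the stated error-rate adjustment reaches only the secondary and other outcomes; if either primary suffices, two-sided family-wise error is about 7.0 to 9.8%, not 5%

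*Protocol article*

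**What the plan says.** Under Primary outcomes, the protocol article states: "The level of depressive symptomatology and a categorical diagnosis of depression after treatment constitute the primary outcomes". The abstract likewise lists both and places them post-treatment. The section on measures of primary outcomes gives each its own instrument: the SCID for diagnosis and the BDI-II for symptoms.

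Under Data collection, management, and analysis, both enter the main comparison: "The main analysis will compare groups in terms of depression level (that is, diagnostic status and symptom intensity"). Results on the other measures are described there as exploratory. The multiplicity statement follows: "When analysis of secondary/other outcomes are performed, the error probability will be adjusted according to the number of group comparisons performed".

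Under Sample size, the calculation has a single test ("planned main statistical test is ANOVA (repeated measures, between factors")) with "α error probability: 0.05" and "statistical power: 0.80". Nothing there is set aside for a second primary outcome.

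Under Trial design, the study is declared a superiority trial with larger gains expected under ED-CT. The outcome that decides superiority is not named.

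**The concern.** A continuous score and a yes/no diagnosis need two separate tests, so the main analysis gives two opportunities for a positive finding. The article does address multiplicity, but the boundary it draws takes in the results it calls exploratory and leaves out the comparison that carries the superiority claim.

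The article does not say what happens if BDI-II is significant and SCID diagnosis is not, or the reverse. If that is settled after the data are seen, the decisive outcome can be whichever one came out favourably, and the nominal 5% no longer describes the trial's error rate.

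**Working it through.** **Inputs from the protocol article.** Two primary outcomes (Primary outcomes). From Sample size: alpha 0.05, power 0.80, *f* = 0.247, two groups, two measurements, correlation between repeated measures 0.50, total of 100, allocation 43 CT and 57 ED-CT.

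**Assumption not in the document.** The correlation *r* between the two test statistics under no treatment effect is not given, so it is varied from 0 to 0.9. Both tests are taken as two-sided; the article does not state this in words, but the planned F test is non-directional.

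**Step 1: reproduce the stated sample size.** For a between-groups F test on repeated measures, the noncentrality is

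λ = *f*² × N × m / (1 + (m − 1) × ρ) = 0.247² × 100 × 2 / 1.5 = 8.13, with 1 and 98 degrees of freedom.

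Power is 80.6% at N = 100 and 79.8% at N = 98, so 100 is the smallest even total that reaches 80%. The stated figure reproduces, and it uses the whole 0.05 for one test. With the actual 43/57 allocation, λ is multiplied by 4 × 43 × 57 / 100² = 0.980 and power is 79.9%.

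**Step 2: family-wise error if either primary suffices.** With independent tests it is 1 − 0.95² = 9.75%. With correlation *r* it is P(|Z₁| > 1.96 or |Z₂| > 1.96) for bivariate normal Z. A false claim in favour of ED-CT is P(Z₁ > 1.96 or Z₂ > 1.96), against 2.5% for one test.

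| Assumed *r* | Any false positive, two-sided | False ED-CT superiority |
|---|---|---|
| 0 | 9.8% | 4.9% |
| 0.5 | 9.1% | 4.5% |
| 0.8 | 7.8% | 3.9% |
| 0.9 | 7.0% | 3.5% |

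**Step 3: family-wise error if both must be significant.** With no effect on either outcome, P(both) = 0.05 + 0.05 − P(either). That is 0.10 − 0.0975 = 0.25% at *r* = 0 and 0.10 − 0.0704 = 3.0% at *r* = 0.9. If one outcome has a real effect and the other does not, the error is at most the 5% of the null one. There is no inflation.

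**Step 4: what the cures do to BDI-II power at N = 100.**
- Fixed order with BDI-II first at 0.05: unchanged from Step 1.
- BDI-II tested at 0.025: 71.7% with equal arms and 70.8% with 43/57. About 120 participants would be needed to regain 80%. This is the floor for BDI-II under Holm, which tests it at 0.05 once the SCID test has passed at 0.025.
- Both must succeed: overall power cannot exceed that of the weaker test, so it cannot exceed the BDI-II figure in Step 1. How far below it falls is unknown, because the article gives no power for SCID diagnosis.

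**The case against.** The strongest objection is that the article never says one significant primary is enough. It describes diagnosis and symptom intensity as two aspects of depression level, which fits a both-must-succeed reading, and then nothing is inflated. This stands, and it is why the error figures are conditional. It does not remove the gap, because the both-must-succeed reading is not written down either.

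A second objection is that a success rule is often left to an analysis plan or full protocol, neither of which is shown, and that promising to adjust secondary outcomes is not the same as declaring the primaries unadjusted. That is fair as to intent. But the article does set the reach of its adjustment, and it allots the full alpha to one test while naming two primaries. Followed as written, it leaves the primary pair without control.

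Three stronger readings are tempting and are not supported:
- A reader might infer that the false-claim rate simply is 8 to 10%. That needs the either-suffices rule and a correlation of at most about 0.75. It also counts false findings in favour of CT, whereas the trial's hypothesis is that ED-CT is better.
- A reader might count the 3-month comparisons as further primary tests. The article places the primary outcomes after treatment and puts follow-up in a separate model, so they do not belong in this family.
- A reader might add weak power for SCID diagnosis. The article gives no expected diagnosis rates, so any such figure rests on an assumed rate, and it has no bearing on type I error.

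**Conclusion.** The point holds in conditional form. The article fixes two primary outcomes, tests both, limits its stated adjustment to the rest and gives no decision rule for the pair. On an either-suffices reading the family-wise error lies between 7.0% and 9.8% for correlations from 0.9 down to 0, and exceeds 5% at any correlation short of perfect. The relative inflation is the same in the direction of interest: at most about double, and about 1.4 times at a correlation of 0.9. On a both-required reading the error is controlled. The document does not say which reading applies, and it does not give the correlation. The remedy is a matter of wording and needs no new participants or data.

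**What to change.** State the primary success rule before unblinding. Any one of these would do:

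1. **Fixed order (least costly).** Test post-treatment BDI-II at two-sided 0.05, and test post-treatment SCID diagnosis at 0.05 only if BDI-II is significant. BDI-II goes first because the sample size rests on a continuous measure, so that calculation stays valid. Cost: a result on SCID diagnosis alone can no longer be claimed as confirmatory.
2. **Holm over the two primaries.** Both keep equal standing. Cost: power for BDI-II can fall to about 72% at N = 100, below the stated 80%.
3. **Both must be significant at 0.05.** No alpha split is needed. Cost: overall power falls below the stated 80% by an amount that depends on the SCID test, for which the article gives no power.

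The multiplicity sentence should then be extended so that it says how the primary pair is handled as well as the secondary and other outcomes.

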### Monitoring study implementation

The management of unintended effects or harm (that is, clinically significant increase in depressive symptomatology, as measured by the BDI-II), is performed by the supervising clinical psychologist employed for this study, who monitors the clinical evaluations and therapy sessions. If necessary, the supervisor can decide to terminate the treatment/clinical assessment and make a further referral.

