#### Eligibility criteria

Romanian-speaking adults (18 years or older) with raised BDI [24,29]) scores (>13), current diagnosis of major depressive disorder or major depressive episode (MDD or MDE), and MDD with comorbid dysthymia, are included in the study. Participants presenting with panic disorder, substance abuse, psychotic symptoms, organic brain disorders (for example, dementia), imminent risk of suicide, self-injury or harming others, or serious legal or health issues that would prevent from regularly attending, are excluded.

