#### Measures of primary outcomes

The Structured Clinical Interview for DSM-IV (SCID) [37], specifically, the Overview, Mood Episodes, and Anxiety Disorders modules, is used for the clinical assessment of depression. The Overview module collects information about sociodemographic variables (date of birth, marital status, number of children, level of education, employment status), drug use, physical and psychological treatment history (including any past or current treatments for depression), and current social functioning. The Mood Episodes and Anxiety Disorders modules follow the diagnostic criteria of the DSM-IV-TR [28] for mood episodes and anxiety disorders. The SCID has been adapted for use on the Romanian population [38].

The BDI-II [24,29], a 21-item version of the original BDI [39], is one of the most widely used self-report measures of depression. Participants rate the intensity of depressive symptoms on a Likert scale from 0 to 3, where 0 corresponds to lack of the symptom, while 3 corresponds to the highest intensity. The psychometric properties of the original BDI are well established, and the BDI-II also appears to be psychometrically strong [24]. The BDI-II has been adapted for use with the Romanian population [40], and has adequate psychometric properties [41].

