### Data collection, management, and analysis

Each eligible patient is assigned a unique identification number and asked to complete the evaluation package, including the primary, secondary, and other outcomes, as well as demographic information (initial assessment). The same set of measures is administered after the final session (post-intervention assessment) and at 3 months after the final session (follow-up assessment). After sessions 4 and 8, patients also complete several measures of primary outcomes (that is, BDI-II), and other outcomes (ATQ, DAS, ABS II, PANAS, B-COPE, treatment outcome expectancies,WAI, CSQ-8, and Intent-to-Attend Scale). In addition, the participants complete the BDI-II, CSQ-8, and Intent-to-Attend Scale after each session.

To ensure high accuracy of data collection, all the measures are completed electronically, via a special system designed to reliably capture and organize the data points while minimizing the risk of missing responses. The system has been especially developed for the purposes of this study, and is secured on a server. Each participant uses their unique identification number to log on to the system. The therapists are responsible for assisting the patients in this process, and providing clarifications when needed.

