To promote participant retention and follow-up completion, several strategies are being used. First, the participants receive a clear and complete description about the project, including, but not limited to, information regarding the type of psychotherapy offered, that is, CT, which is the standard of care in the psychological treatment for depression, having remission rates comparable with medication, and being more efficient than medication alone in the long term. The participants are also informed that the treatment is being provided free by therapists trained in the top-ranked Department of Clinical Psychology and Psychotherapy in the country [96], recently added, through its academic spin-off, the International Institute for the Advanced Studies of Psychotherapy and Applied Mental Health, to the Mapping of the European Research Infrastructure Landscape (MERIL) network [97]. Because in Romania psychotherapy sessions are not reimbursed by health insurance companies, we expect that this financial factor will also act as a motivator for the patient to stay in treatment. Furthermore, the therapy sessions are scheduled in a flexible manner, according to the patient’s preferences. Additionally, the therapist will call the participant the day before the planned session for a brief check, and to ensure continuation in therapy. Most importantly, to ensure retention, at the end of each session the participants complete the ‘Intend-to-Attend’ one-item scale, which is meant to promote commitment to the therapeutic process as well as to detect any issues that might require the therapist’s special attention. Lastly, the therapists carefully prepare the end session of the therapy and explain to the participants that they will keep in touch. The therapists also remind the patients at this time that the free treatment was possible because of a research grant, which makes the collection of follow-up measurements essential.

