### Ethics and dissemination

The study has been approved by the ethics commission at Babes-Bolyai University. As with any study on depression, there are ethical concerns that need to be addressed. First, the exclusionary criteria exclude people who pose an imminent danger to themselves or others. These people will be immediately referred to the appropriate services dealing with such cases. Second, if a patient’s condition worsens during the therapy, the supervising clinical psychologist can opt to terminate the treatment ahead of schedule and make an appropriate referral. Third, people with mental conditions other than depression are also excluded, and will be referred to the services best suited to dealing with their problems.

One arm of this clinical trial involves interventions that stem from an evolutionary understanding of human behavior. The role of the SCSRFQ scale, administered at intake, is to assess the strength of religious beliefs before the first session, when the ED-CT conceptualization takes place. Special care will be taken with the patients whose religious beliefs might make them less receptive to the theoretical framework of such interventions. In such cases, the therapist will be mindful of the patient’s beliefs, and explain the basic tenets of ED-CT in a very sensitive manner.

Finally, confidentiality and privacy are of paramount importance. The completed forms of the clinical instruments are kept in locked cabinets and the access to the electronic data is password-protected. The passwords are changed regularly, and the clinical assessment reports contain no identifying information.

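### Harm is glossed only as a BDI-II rise, so read as written a suicide attempt, self-injury, harm to others or psychiatric admission without such a rise is not counted as harm

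*Protocol article*

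**What the plan says.** Monitoring study implementation assigns to the supervising clinical psychologist the management of "unintended effects or harm (that is, clinically significant increase in depressive symptomatology, as measured by the BDI-II". The supervisor follows the clinical evaluations and therapy sessions and may end treatment or assessment and refer the patient elsewhere.

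Eligibility criteria keeps out people who present with "imminent risk of suicide, self-injury or harming others". Ethics and dissemination repeats this as an entry exclusion and adds, for those already in therapy, that "if a patient’s condition worsens during the therapy, the supervising clinical psychologist can opt to terminate the treatment ahead of schedule".

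Data collection, management, and analysis has the BDI-II completed after each session. For the full package, "The same set of measures is administered after the final session (post-intervention assessment) and at 3 months after the final session". Among the retention measures in the same section, "the therapist will call the participant the day before the planned session for a brief check".

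Measures of primary outcomes says that the SCID Overview module collects "physical and psychological treatment history (including any past or current treatments for depression". Participant timeline states that the clinical assessors stay blinded to condition throughout.

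**The concern.** The gloss ties harm to one self-report symptom scale. An act such as a suicide attempt, or an event such as a psychiatric admission, is not a score and need not come with one. The BDI-II is also a primary outcome measure, so harm defined this way is largely the efficacy measure read in the opposite direction and adds little separate safety information.

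ED-CT adds new components to standard CT, and the Discussion presents the trial as the first controlled attempt of its kind. It also says that a result at least comparable with CT would lead to a further trial. Whether serious events occurred under each treatment ought to inform that step, and a count that followed the present wording could leave them out.

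**Working it through.** No arithmetic applies. The question is what the text includes, so the relevant sections are set side by side.

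1. **The definition.** Monitoring study implementation joins harm to the BDI-II rise with 'that is', which on its face equates the two. The article uses 'for example' where it means an illustration, as with organic brain disorders in Eligibility criteria.

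2. **Any wider definition elsewhere.**
   - Eligibility criteria names suicide risk, self-injury and harming others, but only as reasons not to enter.
   - Ethics and dissemination repeats that exclusion. It then gives the supervisor discretion to stop treatment if a patient worsens. This is an action rule: it names no event and does not enlarge the definition.
   - Participant timeline deals with referral of people who do not qualify.
   - Dissemination policy plans papers on primary outcomes and on mechanisms of change, and says nothing further on harm.
   - Psychiatric admission is not mentioned anywhere as an on-study event.

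3. **Whether the BDI-II would register such an event anyway.**
   - For a participant who keeps attending, scoring after each session gives a fair chance that a deterioration is recorded. It does not guarantee that an act or admission comes with a rise.
   - A participant who has such an event and stops attending may have no later session score.
   - After the post-intervention assessment, the next scheduled BDI-II is at 3 months. Therapists tell participants that they will keep in touch, but no scored contact is listed in between. An event followed by recovery could leave no rise.

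4. **Other routes to detection.** The SCID Overview might reveal an admission for depression if that module is repeated after treatment. The article does not say outright that it is, and does not link it to harm. Therapist calls before planned sessions could also bring events to light, but are described as a retention measure.

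The wording therefore leaves these events outside harm, while several clinical routes could still bring them to the team's notice.

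**The case against.** The strongest reply is that this section is about management, not about a harm report. It sets no rule for recording, tabulating or analysing adverse events, and such rules may well be in the full protocol, which is not at hand. That stands. The absence of a reporting procedure is therefore no finding; what remains is the definition that the article does state.

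A second reply is that 'that is' is used loosely here. Data collection, management, and analysis glosses several primary outcome measures with the BDI-II alone, and describes the therapy offered to participants as CT although one arm receives ED-CT. This weakens the case that the authors meant a closed definition. It does not supply a wider one, and the literal reading is still the natural one.

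A third reply is that session monitoring, BDI-II scoring after each session and the discretion to stop for worsening narrow the gap. They do, and this limits the severity.

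Three stronger readings are tempting, and the documents do not support them:

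- *Patients are left unprotected.* The supervisor's monitoring and power to stop and refer are not confined to BDI-II changes.
- *The trial's harm report will omit serious events.* No harm report is described, so this cannot be asserted.
- *Numbers show that events would be missed.* The BDI-II has 21 items, and "Participants rate the intensity of depressive symptoms on a Likert scale from 0 to 3", so one item can add at most 3 of 21 × 3 = 63 points (4.8%). Given "This resulted in 43 participants randomized to the CT group, and 57 participants randomized to the ED-CT group", one event is 1/57 = 1.8% or 1/43 = 2.3% of an arm. The first figure says nothing without a threshold for clinical significance, which the article does not give. The second is only the reciprocal of an arm size.

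**Conclusion.** The point holds as one of definition. As written, harm is a clinically significant BDI-II rise, and suicidal behaviour, self-injury, harm to others or psychiatric admission without one is not included. Clinical oversight is broader, so the defect lies in what is identified as harm and not in how patients are looked after. The primary outcomes and their analysis are unaffected.

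Severity is minor to moderate. No numerical size is claimed: the article gives no event rate and no share of events that would occur without a BDI-II rise. The conclusion assumes that the gloss is meant literally and that the full protocol does not define harm more widely. If it does, the article's wording only needs to be brought into line.

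**What to change.** Extend the parenthesis in Monitoring study implementation so that harm covers suicidal behaviour, self-injury, harm to others, psychiatric admission and treatment ended for worsening, whatever the BDI-II score. Keep the clinically significant BDI-II rise as one component.

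Have the blinded clinical assessors ask the same short set of event questions in both arms at the planned post-treatment and 3-month assessments, and take counts by arm from those answers. Therapist notes and pre-session calls should serve clinical management and supplement the counts, but not be their main source. Each protocol is delivered by its own two therapists (Assignment to interventions), and therapists cannot be blinded (Discussion), so ascertainment through them could differ between arms. Show beside the counts how many participants in each arm have unknown status.

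The cost is a wording change and a few questions at assessments already planned, assuming that the blinded assessors see participants at both. There is slightly more recording, and the harm picture may be less favourable. Some differential ascertainment can still enter through the therapist sources, and events in participants who never respond will still be missed. Enrolment began on 3 October 2012, so anyone already past an assessment when the change is made would have to be asked at the next one or shown as not asked.
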